### Sample size

In the previous 5‐week pilot RCT, Hedge's g for CES‐D scores between the SPSRS and control groups was 0.61.^25^ However, pilot studies have been shown to overestimate results.^34^, ^35^, ^36^ Therefore, considering a Hedge's *g* of 0.4, a two‐sided significance level of 5%, and a power of 80%, the sample size was calculated at 100 participants per group, totaling 200. Furthermore, internet‐based studies have reported dropout rates of 30%, and a systematic review of RCTs in smartphone apps for depression indicated a dropout rate of 47.8% after adjustment for publication bias.^70^, ^71^ Therefore, assuming a 50% dropout rate, this trial's sample size, using the pwr package in R (version 4.5.1), was calculated at 200 participants per group, totaling 400.

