#### Analysis of primary and secondary outcomes

Data analysis will be based on ITT analysis. Therefore, participants will be analyzed based on their initial group assignment regardless of adherence to the intervention. Assuming primary outcome data are randomly missing, the trial will use a linear mixed model (LMM) with restricted maximum‐likelihood estimation to compare mean changes between the experimental and waiting‐list control groups from baseline to Week 5.^72^ LMM can address defects arising in clinical trials and use all available data to estimate results, thereby making it possible to compare the experimental group that addressed the missing data to the waiting‐list control group.^72^

The CES‐D score is the dependent variable; the independent variables are group (experimental or control), time (baseline, 3 weeks, 5 weeks), and interaction between group and time—all treated as fixed‐effect factors, with participants treated as random‐effect factors. Baseline CES‐D scores will be included as covariates in the LMM. Additionally, to confirm results' robustness for the primary outcome, sensitivity analyses will be conducted using multiple imputation methods and per‐protocol analyses only for participants who provided complete data.^73^ Statistical significance will be set at *p* < 0.05 using a two‐tailed test. Additionally, Hedge's *g* will be calculated as the effect size between the two groups.^74^, ^75^ Secondary outcomes will be analyzed using the same procedures as primary outcomes; however, due to secondary outcomes' exploratory nature, no adjustments for multiple comparisons will be performed. No subgroup analyses are currently planned. LMM calculations will use the lmerTest package, and Hedge's *g*‐statistic will be calculated using the compute.es package. Multiple comparisons will be performed using the mice package.

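### At a planned 50% dropout, neither named sensitivity analysis tests departure from missing-at-random, so agreement between them cannot establish robustness

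*Protocol article*

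**What the plan says.** In the Protocol article, the section on analysis of primary and secondary outcomes compares the arms with a linear mixed model on CES-D at baseline, week 3 and week 5, "Assuming primary outcome data are randomly missing". It names two analyses to support the robustness of the primary result. For the first, "sensitivity analyses will be conducted using multiple imputation methods"; no imputation model and no departure from missing-at-random (MAR) are stated. The second is per-protocol "analyses only for participants who provided complete data"; no adherence criterion is attached.

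The Sample size section plans on "assuming a 50% dropout rate". It also cites dropout of 30% in internet-based studies and 47.8% in a review of smartphone apps for depression.

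Three other sections bear on the point:
- **Interventions (experimental group)** sets a viewing minimum of 350 minutes over five weeks, and **Data collection** says viewing time is recorded.
- **Criteria for discontinuing or modifying allocated interventions** still requests outcome assessments from people who stop the intervention.
- **Plans to promote participant retention** repeats that request, and offers the experimental arm 2300 points on top of the 200 open to everyone, conditional on answering the week 3 and week 5 surveys.

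**The concern.** A sensitivity analysis is informative about an assumption only if it changes that assumption. Here MAR may have to carry up to half of the week 5 data, and neither named analysis relaxes it. MAR-based imputation is largely a second way of computing the mixed-model estimate. Restricting to complete data makes the assumption stricter.

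Missingness could plausibly differ by arm. Only the experimental arm has a daily task to abandon, participants are unblinded, and the reward for answering is 200 + 2300 = 2500 points in one arm against 200 in the other. If the people who go missing are also those who fare worse than their observed scores predict, and this happens more in the experimental arm, all three estimates favour SPSRS together. The trial could then report a result as robust without having tested the assumption it depends on most.

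**Working it through.** **1. The plan's own figure.** The inputs are "considering a Hedge's *g* of 0.4", two-sided 5% and 80% power. The normal approximation gives 99 per group. The exact two-sample t calculation gives 100 per group (power 0.804), which matches "a power of 80%, the sample size was calculated at 100 participants per group, totaling 200". Dividing by one minus the dropout rate, 100 / (1 − 0.5) = 200, which matches "was calculated at 200 participants per group, totaling 400". The sample size is not at issue. The 50% means the plan allows for 100 of 200 week 5 scores to be missing in each arm.

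**2. Size of a departure from MAR.** Let p be the share missing and δ the amount, in SD, by which the unobserved scores are worse than MAR predicts. The overstatement of the effect is

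p(exp) × δ(exp) − p(control) × δ(control).

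Equal shares and equal shifts cancel. If only the experimental arm is shifted, the overstatement is p × δ. The shifts below are assumptions; the dropout rates are two of those the plan cites or uses.

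| δ in experimental arm (SD) | Overstatement at 50% | Overstatement at 30% |
|---|---|---|
| 0.1 | 0.05 | 0.03 |
| 0.2 | 0.10 | 0.06 |
| 0.3 | 0.15 | 0.09 |
| 0.4 | 0.20 | 0.12 |
| 0.5 | 0.25 | 0.15 |

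**3. Tipping point.** Take an observed g of 0.4 with 100 observed per arm.
- SE = √(2/100) = 0.141, so the significance limit is 1.96 × 0.141 = 0.277.
- The shift that removes significance is (0.4 − 0.277) / 0.5 ≈ 0.25 SD.
- The shift that removes the whole effect is 0.4 / 0.5 = 0.8 SD.
- At 30% dropout there are 140 observed per arm, SE = √(2/140) = 0.120, and the shift that removes significance is (0.4 − 1.96 × 0.120) / 0.3 ≈ 0.55 SD.

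The SE is held fixed and ignores the gain from baseline adjustment. A smaller SE would raise these tipping shifts.

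**4. Do the named analyses expose the problem?** A simulation used 600 trials of 200 per arm, a true effect of zero and about 50% missing at week 5. Assumed correlations were 0.6 (baseline to week 3), 0.5 (baseline to week 5) and 0.7 (week 3 to week 5). A MAR likelihood estimate stood in for the mixed model, and the imputation was MAR-based. Entries are mean bias in SD, with Monte Carlo error about 0.005; negative favours SPSRS.

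| Dropout mechanism | MAR likelihood | MAR imputation | Completers |
|---|---|---|---|
| Completely at random | 0.00 | 0.00 | 0.00 |
| Depends on week 3 score, experimental arm only | 0.00 | 0.00 | −0.21 |
| Depends on unobserved week 5 score, experimental arm only | −0.30 | −0.30 | −0.39 |
| Depends on unobserved week 5 score, both arms alike | 0.00 | 0.00 | 0.00 |

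Imputation matches the likelihood estimate in every row. Completers are never less biased, and are worse in rows two and three. In row three all three err in the same direction. The sizes follow from the assumed correlations and dropout slopes; the pattern is what matters.

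**The case against.** Five points can fairly be made for the plan.

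- **The imputation model is not stated.** The article gives the method and the mice package only. An imputation could carry a shift, or use K6, GAD-7 and viewing time, and an analysis plan not shown may say so. This stands as a caution: that imputation will run under MAR is inferred from the absence of any stated departure. But the article itself names the robustness set and its purpose, and announces no such departure.
- **The two analyses do not share one assumption.** A reader might infer that both rest on the primary model's assumption and must agree with it. They need not: completers require more than MAR, and row two above shows them diverging from the model. Such a divergence points to dropout related to earlier scores; it does not test MAR.
- **Stopping viewing is not stopping answering.** People who discontinue are still asked for outcomes, reminders are sent, and the extra points reward answering rather than viewing. Non-users who answer enter the model with their real scores. This stands. It reduces the problem by an unknown amount, while the unequal incentive remains a reason for response to differ by arm.
- **A twofold overstatement is not established.** It can be produced: if half the experimental arm drops out and loses all of a 0.40 SD benefit, the true effect is 0.5 × 0.40 = 0.20, against 0.40 in completers and 0.36 from a simulated MAR likelihood. That is one extreme. If dropouts lose half the benefit, completers show 0.40 against a truth of 0.30. If 30% drop out and lose it all, the truth is 0.28.
- **The mixed model does not contradict intention-to-treat.** Analysing everyone as randomised under MAR is compatible with that aim, and 50% is a planning allowance rather than a forecast.

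On the per-protocol set, a reader might infer that someone with no viewing minutes and full surveys is certainly included. The sentence could also mean an adherent set further limited to complete data. What can be said is that completeness is the only criterion given.

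**Conclusion.** The point holds in a limited form. As described, neither named analysis relaxes MAR, so their agreement with the primary result would say nothing about informative dropout at the planned 50%.

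Bias is a possibility, not a demonstrated fact. It requires dropout that is informative and differs by arm; the same informative mechanism in both arms gave none. Under assumed shifts of 0.1 to 0.5 SD in the experimental arm, the overstatement is 0.05 to 0.25 SD at 50% dropout and 0.03 to 0.15 SD at 30%. An observed g of 0.4 would lose significance at a shift of about 0.25 SD at 50% dropout. The documents give no basis for choosing one value in that range.

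The per-protocol issue is one of labelling. The sentence that assigns mice to multiple comparisons is a clerical slip, evidently for multiple imputation.

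**What to change.** - Keep the mixed model as the primary analysis.
- Prespecify, as the robustness analysis, a delta-adjusted imputation in mice with shifts varied separately by arm up to the tipping point, a control-based (jump-to-reference) imputation for experimental-arm non-responders, or both. State beforehand, in CES-D points, which shifts count as plausible, and claim robustness only against these analyses.
- State the imputation model, and correct the sentence on mice to multiple imputation.
- Relabel the complete-data analysis as a completer analysis. If a per-protocol analysis is kept, define it by logged viewing time and report it as supplementary. It selects on behaviour after randomisation in one arm and does not test the missing-data assumption.

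The cost is some analysis text and a little more programming, with no change to sample size or data collection. The sensitivity results may look less favourable, and jump-to-reference is deliberately conservative because it gives experimental non-responders no benefit. Recruitment is scheduled to March 2030, so there should be time to fix this before the data are analysed.

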#### Estimating appropriate intervention time for SPSRS

The estimation of the appropriate SPSRS intervention time will use data from the experimental group. Each participant's reliable change (RC) in depressive symptoms will be defined as a change in the CES‐D score (baseline to 5 weeks) that exceeds the minimal important change (MIC). The appropriate SPSRS video‐viewing time will be estimated by the receiver operator characteristic (ROC) method, which calculates the area under the curve, sensitivity, specificity, and the Youden index.^76^ The maximum Youden index point will be the optimal SPSRS intervention time. A previous study has estimated the CES‐D score's MIC; however, the MIC may vary depending on the disease, the intervention, the follow‐up period, and the estimation method.^77^, ^78^, ^79^ Therefore, the CES‐D score's MIC used as this trial's RC will be estimated using a predictive modeling method anchored to the GRC scales after the experimental group's 5‐week intervention.^78^, ^79^ The ROC method will be implemented with the pROC package, and the predictive modeling method will be conducted with the stats package.

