### Identifying optimal intervention timing to enhance SPSRS intervention's efficacy

If SPSRS proves efficacious in reducing StD's depressive symptoms, estimating its appropriate intervention duration is crucial, especially because its video‐viewing time has not yet been sufficiently established. Identification of appropriate intervention duration not only enables theoretical refinement of the therapeutic mechanism and SPSRS process but can also help clarify its clinical implementation. Therefore, the trial's secondary objective is to explore an appropriate intervention duration.

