### Interventions

#### Experimental group

The experimental group will receive a video‐viewing intervention using SPSRS, which allows participants to search for videos by keyword and watch them (similar to YouTube).^16^ To enable participants to access YouTube videos, SPSRS utilizes the YouTube API. Thus, to leverage SPSRS's benefits, participants will choose which videos to watch and enjoy.

The key difference between SPSRS and video‐viewing sites like YouTube is that SPSRS presents two types of word stimulation during the video. First, a confidence‐boosting word or phrase randomly appears (17 ms) in one of the screen's four corners: *can*, *let us try*, *good luck*, *able*, or *do not worry*.^17^ Immediately afterward, a positive word appears (150 ms) at the screen's center: *nice*, *great*, *fantastic*, *satisfactory*, or *enjoyable*.^18^ These words repeat every 5 s. The experimental group will engage in SPSRS video‐viewing for at least 10 min per day (at least 70 min per week; at least 350 min over 5 weeks), determined based on the previous pilot RCT.^25^

This trial will undoubtedly enroll participants with diverse preferences in video content, and each individual is free to select videos that interest them so that the intervention is applicable to a wide adult demographic. However, as the SPSRS utilizes videos from YouTube, participants will not have access to videos that violate YouTube's Community Guidelines (e.g., due to violent, sexual, or fraudulent content). Additionally, participants may pause or stop the video at any time if they experience discomfort or health effects while watching. While the SPSRS system does not currently have its own reporting function, users can directly navigate from the SPSRS video playback screen to YouTube and report violations.

Participants will receive the SPSRS link and instructions for its use via email. To increase adherence, a templated text reminder will be sent once a week.^25^, ^52^ Additionally, SPSRS not only displays the daily required viewing time on the home screen but also allows participants to check their current viewing time via the history function.

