### Allocation

Following baseline assessment, participants will be randomly assigned to the experimental group or the waiting‐list control group in a 1:1 ratio. The randomization list will be generated by an independent third party using the blockrand package in R (version 4.5.1) with a replacement block method of appropriate size. To ensure allocation concealment, the block size will not be disclosed until the trial ends. The generated randomization list will be managed at the Central Registration Center at Kagoshima University, and participants will be randomly assigned after completing the baseline questionnaire. These procedures will prevent selection bias.

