### Data collection

Table 1 shows the outcome assessments' schedule. Information regarding depressive symptoms (primary outcome), psychological distress, and anxiety symptoms will be collected at baseline, 3 and 5 weeks after the intervention begins. Additionally, as a baseline assessment, demographic data will be collected via online questionnaires: gender and age, lifestyle characteristics including sleep duration and exercise, drinking, and smoking habits. To protect users' privacy, the research team will not track the specific video content viewed by participants. Instead, only participants' video‐viewing time will be collected using the SPSRS video‐viewing time recording site managed by the principal investigator. To prevent missing data, the questionnaires are set to reject incomplete responses automatically.

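### The Youden cut-off on self-chosen viewing time in the experimental arm is an association and cannot support the label of optimal intervention time

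*Protocol article*

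**What the plan says.** In the protocol article, *Identifying optimal intervention timing* makes this a lower-tier aim: the trial's "secondary objective is to explore an appropriate intervention duration". It is conditional on SPSRS first proving efficacious. The same paragraph expects the result to refine the account of how the therapy works and to guide its clinical use.

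*Estimating appropriate intervention time for SPSRS* fixes the method. "The estimation of the appropriate SPSRS intervention time will use data from the experimental group". The outcome is "a change in the CES‐D score (baseline to 5 weeks) that exceeds the minimal important change (MIC"), with the MIC estimated in the same arm from the week-5 global rating of change. An ROC analysis on viewing time follows, and the maximum Youden point is declared the optimal time. The section sets no condition on the AUC or on the precision of the cut-off.

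The exposure is described elsewhere:

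- *Allocation*: "participants will be randomly assigned to the experimental group or the waiting‐list control group in a 1:1 ratio". Only the arm is randomised.
- *Experimental group*: one target for all, "at least 10 min per day (at least 70 min per week; at least 350 min over 5 weeks"). It is a minimum with no upper limit, backed by weekly reminders and a display: "SPSRS not only displays the daily required viewing time on the home screen".
- *Experimental group*: "participants may pause or stop the video at any time if they experience discomfort or health effects while watching".
- *Data collection*: "only participants' video‐viewing time will be collected using the SPSRS video‐viewing time recording site". Neither the window nor the summary of viewing time (total or daily mean, for example) is stated.
- *Blinding*: participants are not blinded. CES-D and the global rating are self-reported.

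**The concern.** With one target for the whole arm, differences in minutes are differences in adherence. Two non-causal routes connect adherence to improvement:

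- **Shared cause.** Motivation or expectancy can raise both viewing and self-rated improvement.
- **Reverse causation.** Someone who feels better by week 3 may keep watching, and someone who does not may stop. If viewing is summed over the 5-week intervention, which is the natural reading, it overlaps the baseline-to-week-5 outcome, and improvement can come before part of the exposure it is meant to result from.

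The ROC curve cannot tell either route from a true effect of minutes. Requiring an AUC above 0.5 would not help, because both routes produce an AUC that really is above 0.5. What is at stake is an adherence artefact being published as a recommended duration.

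**Working it through.** **1. Number available.** *Sample size* uses g = 0.4, two-sided 5% and 80% power. The normal approximation gives 2 × (1.960 + 0.842)² / 0.4² = 98.1, so 99 per group. The t-test solution is 99.08, so 100. Allowing for 50% dropout, 100 / (1 − 0.5) = 200 per group. The plan's figures reproduce, and about 100 experimental participants would remain for the ROC analysis.

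**2. Shared cause, no effect of minutes.** The documents give no viewing distribution and no correlation, so these inputs are assumptions:

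- trait m ~ N(0, 1); minutes = 350 × exp(0.4 m);
- latent improvement = ρ m + √(1 − ρ²) e, with e ~ N(0, 1) independent of m;
- a participant exceeds the MIC if latent improvement lies in the top 30% or top 50%;
- AUC = U / (n₁ n₀), tested by Mann–Whitney; Youden J = sensitivity + specificity − 1; 4,000 runs per setting.

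Results at n = 100 (30% / 50% exceeding the MIC):

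| ρ | mean AUC | p < 0.05 | mean max J |
|---|---|---|---|
| 0 | 0.50 / 0.50 | 5% / 5% | 0.13 / 0.12 |
| 0.2 | 0.59 / 0.59 | 32% / 35% | 0.23 / 0.22 |
| 0.3 | 0.64 / 0.64 | 62% / 65% | 0.29 / 0.28 |
| 0.5 | 0.74 / 0.73 | 97% / 99% | 0.42 / 0.40 |

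Separate runs with 40% exceeding the MIC gave AUCs of 0.59, 0.64 and 0.68 at ρ = 0.2, 0.3 and 0.4. The confidence interval excluded 0.5 in 35%, 66% and 90% of trials.

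The rule returned a cut-off in every trial. At ρ = 0 the 5th to 95th percentiles of that cut-off ran from about 181 to 692 minutes, which is noise. Its centre near 350 follows from the assumed median and predicts nothing. With no dropout (n = 200) the false signal is found more often: 56–61% at ρ = 0.2 and 89–93% at ρ = 0.3.

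**3. Reverse causation, no effect of minutes.** Improvement by week 3 drives later viewing. In one set of assumptions the total-time AUC was 0.63 and 64% of trials excluded 0.5. Other assumptions gave AUCs of 0.55–0.61 (14–47% of trials) and 0.60–0.65 (40–71%).

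**4. Would time ordering repair it?** A landmark regression takes week-5 CES-D on minutes viewed to week 3, adjusted for baseline and week-3 CES-D. Under reverse causation alone it rejected in 6% of trials in the first setting of step 3 and in about 4–5% in the others, close to nominal. Under a persistent shared motivation it did not hold. False rejection was about 9% in one setting that added a shared cause to reverse causation, 28–69% in another (correlations 0.21 to 0.37) and 37–86% in a third. In the 28–69% set-up, a real effect of minutes with similar correlations (0.19 to 0.37) was detected in 23–61% of trials, so the regression does not separate confounding from effect.

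**The case against.** The strongest reply is that little depends on this analysis. It is labelled exploratory and conditional on efficacy, and no sample size, alpha or confirmatory conclusion uses it. That stands, and it limits the severity. A reader might infer that the efficacy result is compromised. The documents do not support this: the primary mixed model compares randomised arms and does not use viewing time.

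A second reply is that an article may leave covariate adjustment and the exposure summary to a fuller plan. That also stands, and neither omission is counted here. In particular, a reader might take it as stated that exposure and outcome share one window. Only the outcome window is stated; the overlap is inferred from the 5-week intervention. The objection to the decision rule survives, because the data source, method and rule are all written down, and no extra detail within them turns self-chosen minutes into an assigned duration.

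Third, the *Discussion* concedes possible performance bias from lack of blinding. It does so for the contrast between groups. None of its nine limitations mentions self-selected viewing within the arm or reverse causation.

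Fourth, a reader might conclude that a landmark regression should replace the ROC analysis. Step 4 argues against that. The regression also removes benefit already gained by week 3, yields a slope and not a time, and needs dated viewing records that the article does not describe.

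**Conclusion.** The concern holds as a limit on interpretation. Followed exactly, the plan would name an optimal duration from one arm's self-selected adherence, a figure that could arise with no effect of minutes. At 100 participants, assumed shared-cause correlations of 0.2 to 0.4 give a mean AUC of about 0.59 to 0.68, nominally significant in about 35% to 90% of trials. These figures are illustrative. They rest on the assumed correlation, viewing distribution and share exceeding the MIC, and the documents cannot show how large the bias would be in this trial. The design point does not depend on them: without randomised durations, the result is an association. The correction should be made because the text ties the figure to mechanism and clinical implementation, even though the aim is secondary.

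**What to change.** - In *Identifying optimal intervention timing* and *Estimating appropriate intervention time for SPSRS*, replace the terms appropriate and optimal intervention time with *viewing time associated with improvement in the experimental arm*.
- State there that the ROC and Youden result is descriptive and non-causal, and that duration can be established only by randomising it.
- Add self-selected viewing and reverse causation to the limitations in the *Discussion*.
- If viewing records are dated, add as a sensitivity analysis only, not as the main analysis, a regression of week-5 CES-D on minutes viewed to week 3, adjusted for baseline and week-3 CES-D. State that it addresses reverse causation but not confounding by motivation, and that it excludes benefit gained before week 3.

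The cost is wording plus, optionally, one regression. Week-3 CES-D is already collected; whether viewing records are dated is for the sponsor to confirm. Recruitment, treatment and the primary analysis do not change. The downside is a weaker claim about duration.

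### The maximum-Youden viewing time is declared the optimal intervention time without any requirement that viewing time be associated with response

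*Protocol article*

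**What the plan says.** The Introduction of the protocol article, in the section on optimal intervention timing, says that the trial's "secondary objective is to explore an appropriate intervention duration". It raises the question conditionally: "If SPSRS proves efficacious in reducing StD's depressive symptoms, estimating its appropriate intervention duration is crucial".

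The Statistical analysis section on estimating intervention time fixes the method. The estimation "will use data from the experimental group". A participant counts as a responder if the CES-D change from baseline to 5 weeks is larger than a minimal important change (MIC), itself estimated in the same arm against the global rating of change. Viewing time is then put through a ROC analysis, "which calculates the area under the curve, sensitivity, specificity, and the Youden index". The decision rule closes the description of the ROC step: "The maximum Youden index point will be the optimal SPSRS intervention time".

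Under Interventions, everyone in the arm has the same instructed minimum, "at least 350 min over 5 weeks", and can see the daily target and their own running total.

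**The concern.** A Youden cut-off is the viewing time that best separates responders from non-responders among the times that happened to occur. It is not, in general, the duration at which benefit is sufficient or greatest. The rule has no exit: whatever the AUC, some time maximises the index, and the text calls that time optimal.

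There is also a design limit. Every participant has the same target, so differences in viewing time are self-chosen after randomisation. People who feel better may watch more, and people who feel worse may stop. There is no randomised contrast between durations.

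The article says that the result can help clarify clinical implementation. A specific number of minutes, published as optimal, could be taken up as a recommendation although it reflects mainly how long this sample watched.

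**Working it through.** **Sample available.** The article's figure reproduces. The normal approximation, n = 2(1.960 + 0.842)² / 0.4² = 98.1, gives 99 per group. The two-sample t-test gives 99.08, rounded up to 100. With 50% dropout, 100 / (1 − 0.5) = 200 per group. The ROC analysis would therefore have about 100 participants with a week-5 score, and at most 200. The article gives no figure for the Youden procedure itself.

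**What the rule estimates.** Let X be viewing time, R response, p(x) the response probability at time x, and π the overall response rate. Then

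J(c) = Pr(X > c | R = 1) − Pr(X > c | R = 0).

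Setting the derivative to zero gives p(c) / π = (1 − p(c)) / (1 − π), that is p(c) = π. Under a smooth rising curve, the maximum-Youden point is where the curve crosses the *average* response rate of this sample. That average depends on how long the sample watched. With no dose effect, J(c) = 0 everywhere and the sample maximum is noise.

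**Assumptions (none from the documents).** n = 100; ln(minutes) normal with mean ln 350 − 0.1 and SD 0.5, so the median is 350 × e^(−0.1) = 317 min. Without a dose effect, response probability is 0.45. With one, logit p = −1.2 + minutes/350. ROC direction is either fixed (more viewing predicts response) or set automatically from the data.

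**Result 1: no dose effect.**

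| ROC direction | 5th–95th percentile of cut-off | Apparent Youden ≥ 0.15 |
|---|---|---|
| Fixed | about 146–728 min | 28% of trials |
| Automatic | about 189–524 min | 52% of trials |

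The centre across trials is the sample median. For comparison, the assumed viewing times have a 5th–95th percentile range of 317 × exp(±0.822) = 139–721 min, so with a fixed direction the null cut-off can fall almost anywhere in the sample.

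Other assumed distributions were tried with automatic direction: log-normal with medians 200, 350 and 700 min, uniform on 0–700, and a pile-up just above 350; 30% or 50% responders; n = 100 or 200. The centre was always at the 49th–51st percentile of viewing time, and the 5–95% range at about the 15th–85th percentile. Doubling n did not narrow it.

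**Result 2: one fixed rising curve, viewing times scaled ×0.5, ×1 and ×2.**

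| Sample median viewing | Median cut-off, automatic | Median cut-off, fixed |
|---|---|---|
| 158 min | 168 | 178 |
| 317 min | 345 | 348 |
| 633 min | 635 | 639 |

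The identity p(c) = π explains this. Averaging the curve over each distribution gives π ≈ 0.337, 0.455 and 0.659. Solving c = 350 × (1.2 + logit π) gives 350 × (1.2 − 0.677) ≈ 183, 350 × (1.2 − 0.180) ≈ 357 and 350 × (1.2 + 0.659) ≈ 651 min. The curve is the same in all three cases; only the sample's viewing habits differ.

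**Result 3: a true step at 350 min** (response 30% below, 60% above; log-normal viewing, log-SD 0.6). For sample medians 200, 350 and 700 the median cut-off was 294, 350 and 522 at n = 100, and 317, 350 and 462 at n = 200. The step is found when it lies mid-sample. Otherwise the cut-off is pulled towards the sample median.

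**The case against.** The strongest defence is that the article does not oversell this analysis. It calls the objective exploratory, takes it up only if the intervention proves efficacious, and calculates the AUC, sensitivity and specificity, so a weak result would be visible. Under no effect with automatic direction at n = 100, the AUC has median 0.54 and 95th percentile 0.61. A condensed article may also leave intervals, bootstrapping and missing-data handling to the analysis plan. All of this is fair, and the absence of those details is not criticised here. But the efficacy condition concerns the comparison between groups and does not show that minutes matter, and the AUC is calculated without being used. The sentence that names the cut-off optimal is unconditional.

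Four stronger readings are tempting and not supported:

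- *The cut-off tracks the sample median even with no effect.* Only its centre over repeated trials does. One trial's cut-off scatters widely.
- *The method can never answer the objective.* A true step in mid-range would be roughly recovered, and the 350-minute target makes that a plausible centre. The article neither assumes nor tests for a step.
- *Regression to the mean after selection on CES-D, or estimating the MIC in the same people, biases the cut-off.* Either could matter, but no bias has been quantified. Regression to the mean unrelated to viewing time would mainly dilute discrimination.
- *The trial's main result is compromised.* It is not; the primary mixed-model comparison does not use viewing time.

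**Conclusion.** The point holds in a limited form. The article labels a descriptive, sample-dependent separator as the optimal intervention time without requiring evidence of association. Under the stated assumptions the 5–95% range with no dose effect spans several hundred minutes, and one unchanged rising curve gives cut-offs from about 168 to 635 min as the sample's median viewing moves from 158 to 633. The exact minutes depend on assumed viewing times, responder rates and ROC direction. Two things do not depend on them: the rule always returns a time, and under a smooth rising curve that time depends on the viewing distribution. Because viewing time is self-selected within one arm, a demonstrated association would still not show that longer viewing causes response. This should be changed before analysis, but it concerns an exploratory objective only.

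**What to change.** Make the main analysis for this objective a regression of continuous week-5 CES-D on viewing minutes (spline or log scale) in the experimental arm, adjusted for baseline CES-D and the collected demographics, with 95% bands, and report it as an association. Adjustment does not remove confounding or reverse causation, and the text should say so.

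If the ROC analysis is kept:

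- call the Youden point a descriptive cut-off;
- fix the ROC direction in advance;
- give a bootstrap interval that re-estimates the MIC in each resample;
- make no claim of an optimal time unless the AUC interval excludes 0.5, and even then do not read the cut-off as a causal dose.

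The cost is analysis text and code, with no new data. The downside is that the secondary objective may end without a single recommended time.
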